## Results

Figure 2 depicts the process by which infants from the APTS study were included in the TITANS study.

**Figure 2 FIG2:**
[figure not shown]
Flowchart of all infants randomized in APTS and included in TITANS. The top blue box summarizes all infants randomized and included in APTS. The second blue box summarizes the TITANS follow-up, numbers are to be inserted when data collection is complete. APTS: Australian Placental Transfusion Study; TITANS: Transfusions in the APTS Newborns Study; USA: United States of America

In this section, we will report the final sample size and the total number of infants data missing from the analysis. We will describe the characteristics of participants included in the mediation analysis. Both the total effect and the indirect mediation effects will be reported. All effects will be reported with 95%CI. An example template to represent our results if causal mediators are statistically independent is depicted in Figure 3. To supplement the summary of the direct and indirect effects, we will also report the relevant estimates for the specific exposure-mediator and mediator-outcome relationships. Finally, we will report the sensitivity analyses described in the data-analysis plan that assess how robust our model is to violations of its assumptions.

**Figure 3 FIG3:**
[figure not shown]
Example figure depicting the causal mediation findings if we determine multiple causally independent mediators (M1 is independent of M2) influence blood transfusions. ACME: average causal mediation effect; ADE: average direct effect

## Discussion

Blood transfusions of neonates have been associated with a number of serious adverse outcomes [29]. Nevertheless, there are few evidence-based methods to reduce transfusion exposure [30]. The APTS study found that DCC was associated with a statistically significant reduced need for red cell transfusions by about 10% compared to ICC [15]. However, the mechanism remains unclear. 

The study will, at a minimum, provide further information that should increase clinicians’ understanding of the pathways by which DCC (or other methods to accomplish placental transfusion) results in beneficial patient outcomes. Since one of the main barriers to implementation is lack of understanding about the mechanisms by which such a simple practice change should have such dramatic effects, this should improve adherence to recommendations to defer cord clamping for most babies, thereby reducing mortality and transfusion incidence.

By elaborating on the mechanisms, it may also provide good evidence for how other routine neonatal intensive care practices and interventions affect likelihood of needing to transfuse. Better understanding of these effects may lead to other testable hypotheses or improvements in other aspects of practice, further reducing transfusion exposure and improving other outcomes.

Potential limitations of the study include the dependence on some routinely collected clinical data, which were not collected at the time by the original study according to predefined research definitions. However, we have no reason to think that potential problems of data quality would have been influenced by study group allocation and so do not anticipate that this will be a source of bias.

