## Abstract

Background

Neonates, particularly if born preterm or with congenital anomalies, are among the pediatric patients most likely to need blood transfusion. However, they are also particularly vulnerable to adverse consequences of blood transfusion. Aiming to clamp the umbilical cord for at least a minute after birth is a simple safe procedure that is being increasingly adopted worldwide, although may be associated with increased rates of polycythemia and jaundice. It may also reduce the proportion of preterm babies who need a blood transfusion. The mechanisms for this are not fully understood. Potential mechanisms could include an increased volume of blood transfusion from the placenta to the baby after birth, and an overall reduction in the severity of illness in the first weeks after birth, which could lead to fewer blood tests and greater tolerance of anemia, or enhanced erythropoiesis.

Objectives

To investigate the mechanism behind the reduced need for blood transfusions after deferral of cord clamping.

Methodology

This protocol outlines the methods and data analysis plan for a study using nested retrospective data from a large randomized trial combined with additional data collected from patient medical and pathology records. The additional data items to be collected all relate to the receipt of transfusion and the factors that affect the risk for transfusion in preterm babies. The analysis will include all randomized babies from Australia and New Zealand for whom data are available. Causal mediation analysis is planned to estimate the effects of mediators on the relationship between the timing of cord clamping and the need for blood transfusion. The analysis is designed to discern whether initial severity of illness or the magnitude of placental transfusion mediates red blood cell transfusion dependence.

Anticipated outcomes and dissemination

We expect the study will identify potential strategies for reducing blood transfusions and associated negative outcomes in preterm infants. This will be relevant to researchers, clinicians, and parents. The results will be disseminated through publications, presentations, and inclusion in evidence-based guidelines.

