The intervention consisted of either immediate or delayed cord clamping (as assigned in APTS). Immediate clamping was defined as clamping the cord within 10 seconds of delivery. Delayed clamping was defined as clamping the cord at least 60 seconds after delivery, with the infant held as low as possible, below the introitus or placenta, and with no palpation of the cord. Variations in the protocol were allowed if they would aid the mother, baby, or both. If the baby was non-vigorous (heart rate <100 beats per minute, low muscle tone, or lack of breathing, or crying), clinicians were allowed to break protocol using their discretion. Cord milking was not part of the protocol for either intervention. Further details may be sourced from the original APTS publication [15].

Outcomes

The primary outcome is the proportion of babies receiving red cell transfusion (for restoration of hemoglobin or blood volume). The secondary outcomes are number of transfusions per baby, cumulative transfusion volume (mL/kg) per baby, and primary reasons for each transfusion.

Putative Mediators

M1: Indicators of placental transfusion to be assessed will be hematocrit (on admission, highest on the first day, highest in the first week collected before any postnatal transfusion).

M2: Indicators of initial severity of illness to be assessed will be cumulative blood sample volume collected throughout hospital stay (number of blood tests multiplied by hospital’s usual sample volume for each type of test), sampling line (umbilical arterial line or peripheral arterial line) - yes/no and total duration, mechanical ventilation or inspired O2, and blood pressure.

Sensitivity Analyses (For the Primary Outcome Analysis Only)

Sensitivity analyses will adjust for the following variables: gender, birth <27 weeks vs. ≥27 weeks, method of delivery (vaginal versus cesarean), intraventricular hemorrhage (IVH) (yes/no and grade III/IV yes/no), surgery for patent ductus arteriosus (PDA), necrotizing enterocolitis (NEC), and sodium in the first 24 hours of life. We will also test model assumptions relating to sequential ignorability and post-randomization confounding (discussed further in the data analysis plan).

Potential Confounders (Covariates)

The following covariates may be used for adjustment in the analysis: gestational age at randomization before birth and any oral iron supplement pre-transfusion.

Timing of Assessments

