Putative mediating variables will only be analyzed if they have been measured before the outcome and will be excluded if there is not adequate time and date information available. If the multiple mediator model is applied, careful consideration of timing information will be evaluated. If there is insufficient empirical information to conclude the causal ordering of mediators (M1 causes M2), we will adjust our analytic approach (as discussed in the analysis plan) and discuss any limitations.

Data Analysis Plan

The analysis will include all babies who were initially randomized in the APTS trial for whom we were able to obtain the relevant data and be based on intention-to-treat. All statistical analyses will be conducted in R version 4.1.3 (2022-03-10; R Foundation for Statistical Computing, Vienna, Austria). Descriptive characteristics for continuous data will be presented as means or medians, as appropriate, and categorical data will be presented as frequencies and percentages.

A model-based inference approach will be applied to estimate the average causal mediation effect (ACME), average direct effect (ADE), and the average total effect as recommended [23-25]. This approach will be applied with the R “mediation” package [26]. We will initially fit two models, one model with mediation as the dependent variable and intervention as the independent variable (mediator model), and a second model with the outcome as the dependent variable, and both mediation and intervention as independent variables (outcome model). To account for the clustering of multiples, estimates will be calculated with generalized estimating equations with a compound symmetric correlation structure to account for within subject correlations. Depending on the outcome (binary, count, skew) these will be modelled with the appropriate family and link functions.

A counterfactual framework will be applied to the mediator and outcome models to simulate the values of the mediator and outcome to estimate the potential values of the mediator. This process is used to estimate the ACME, ADE, and average total effects; 95%CI will be estimated with 1000 bootstrap simulations.

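### Mediator error unrelated to study arm leaves the total effect unbiased but generally biases the ACME and ADE, so the Discussion's reassurance does not cover what the study estimates

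*Protocol article*

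**What the plan says.** The limitations paragraph of the Discussion acknowledges "dependence on some routinely collected clinical data, which were not collected at the time by the original study according to predefined research definitions". It sees no reason for quality problems to have been "influenced by study group allocation and so do not anticipate that this will be a source of bias".

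The Data Analysis Plan sets out to "estimate the average causal mediation effect (ACME), average direct effect (ADE), and the average total effect". It uses a mediator model and an outcome model that contains both arm and the measured mediator. The Abstract gives the purpose as to "discern whether initial severity of illness or the magnitude of placental transfusion mediates red blood cell transfusion dependence".

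Under Putative Mediators, placental transfusion (M1) is represented by hematocrit at three time points. Initial severity of illness (M2) is represented by ventilation or inspired oxygen, sampling line (yes/no and duration), blood pressure, and a cumulative sample volume built as "number of blood tests multiplied by hospital’s usual sample volume for each type of test".

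The sensitivity analyses described under Data Analysis Plan and Methodological Assumptions cover adjustment variables, missing data, unmeasured mediator-outcome confounding and non-adherence. None concerns error in the mediator.

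**The concern.** Arguing from no difference by arm to no bias is sound when the question is whether mediator error distorts the randomised comparison, because the total effect does not use the mediator. It fails once the mediator becomes a regressor. The outcome model must estimate the mediator's slope within arm, and noise in a regressor flattens its slope even when the noise is identical in both arms. The part of the effect no longer credited to the mediator is credited to the arm.

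The study asks which of two mechanisms carries the effect and whether a direct effect remains (Objectives 1 to 4). The Introduction links the answer to whether early top-up transfusion could be justified. If two mechanisms are measured with different fidelity, their apparent ranking can partly reflect that difference. As written, the article tells readers not to expect this.

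**Working it through.** The article gives no bias figure to reproduce, so the check is whether the stated inference holds for the planned estimands.

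**Closed form (linear, one mediator).** Let a be the effect of arm on the mediator, b the mediator's slope on the outcome, and d the direct effect. The recorded mediator is the true one plus independent noise, and r is its within-arm reliability (true variance divided by recorded variance).
- Arm to recorded mediator: a, unchanged.
- Slope on the recorded mediator: r × b.
- Estimated indirect effect: r × a × b.
- Estimated direct effect: d + (1 − r) × a × b.
- Total: d + a × b, unchanged.

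**Binary outcome, two-model structure as planned (simulation, 400,000 babies).** Inputs from the article: hematocrit difference +2.7 points (Introduction), and a transfusion reduction of about 10% (Discussion), read here as absolute, which is an assumption. Other assumptions: within-arm hematocrit SD 7, ICC transfusion risk about 0.63, log-odds −0.10 per hematocrit point, direct log-odds −0.2.

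| Reliability | ACME | ADE | Total | Mediated |
|---|---|---|---|---|
| 1.0 | −0.0593 | −0.0437 | −0.1030 | 58% |
| 0.9 | −0.0532 | −0.0498 | −0.1030 | 52% |
| 0.8 | −0.0473 | −0.0558 | −0.1031 | 46% |
| 0.7 | −0.0416 | −0.0615 | −0.1031 | 40% |
| 0.5 | −0.0291 | −0.0740 | −0.1031 | 28% |

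The closed form agrees. At r = 0.7, the ACME is 0.7 × (−0.0593) = −0.0415 and the ADE is −0.0437 + 0.3 × (−0.0593) = −0.0615.

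**Sign of the direct effect.**
- Direct coefficient set to zero: reliability 0.7 produced an ADE of −0.0184 out of a total of −0.0585.
- Direct effect opposite in sign to the indirect effect: the ADE went from +0.0434 to +0.0259, with the total near −0.014. It is pulled toward the total effect, which here makes it smaller.

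**Binary mediator.** Assumed prevalence 65% (ICC) and 55% (DCC). With 90% sensitivity and specificity, the indirect effect went from −0.041 to −0.025 and the direct effect from −0.039 to −0.055. The total stayed at −0.080.

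**Two equally strong mediators (linear, joint model).** Each true indirect effect is 0.39 × 0.08 = 0.0312 in size.
- Uncorrelated, reliabilities 0.9 and 0.5: −0.0280 and −0.0159. The direct effect moved from −0.0330 to −0.0517. Separate single-mediator models gave almost the same indirect effects (−0.0281 and −0.0159).
- Uncorrelated, reliabilities swapped: −0.0156 and −0.0281, so the ranking reverses.
- Correlated at −0.3, reliabilities 0.9 and 0.5: −0.0320 and −0.0154, against −0.0309 and −0.0312 without error. The better-measured mediator came out slightly above its error-free value, despite its own error.

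**Berkson-type error.** If true sample volume scatters around an assigned value (test count × usual volume), a linear model gave indirect effects of −0.0280 with true volume and −0.0278 with assigned volume at 30% scatter. There was no material bias.

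**The case against.** **The statement is brief and hedged.** It is one Discussion sentence, it says only that bias is not anticipated, and it sets no analysis rule. The article also plans range and consistency checks and uses several indicators per mechanism. All true. But the sentence gives a reason, and that reason is invalid for the ACME and ADE. An unseen analysis plan could add a sensitivity analysis, but it would not make the stated inference correct.

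**Severity is measured worse, so the study will favour placental transfusion.** A reader might infer this, because hematocrit is a laboratory value and the severity indicators come from charts. The documents do not support it. Hematocrit is only an indicator of placental transfusion, so assay precision is not its reliability for that mechanism. Some severity indicators, such as whether a sampling line was placed, are plain chart facts. No reliability is given for any variable, and swapping the assumed values swaps the ranking.

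**Sample volume as the example.** The usual-volume construction looks like an obvious source of attenuation, but part of its error may be Berkson-type, which may cause little bias. Miscounted tests or a wrong site volume are not of that type. In Table 1 this indicator appears only in single-mediator model 2.3, so the transfer of effect between correlated mediators does not arise for it.

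**A blanket rule that the ACME shrinks and the ADE grows.** This is also too strong. The ADE can shrink when signs differ, and a better-measured correlated mediator can be overstated.

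**Conclusion.** The concern holds in limited form. For mediator error, independence from study arm protects the total effect of randomised cord clamping, but not the ACME and ADE. Classical error or misclassification generally attenuates the affected mediator's indirect effect and pulls the ADE toward the total effect. With correlated mediators in one model, part can move to the better-measured one.

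The size is not known. Over assumed reliabilities of 0.9 to 0.5, the illustrated mediated share fell from a true 58% to between 52% and 28%. Those figures rest on assumed variances, risks and coefficients and show only that the bias need not be small. Measurement quality could change which mechanism appears to dominate, but the documents do not show which one would gain. Error in the recorded transfusion outcome is a separate matter that was not assessed here.

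**What to change.** 1. Limit the Discussion sentence: mediator error unrelated to allocation is not expected to bias the total effect. Add that such error can bias the ACME and ADE, in a direction and by an amount that depend on the type of error, the signs of the effects and the correlation between mediators.
2. For the primary outcome and the main mediator models, recompute the ACME and ADE over an assumed range of error. Use regression calibration or SIMEX over a reliability range for continuous mediators, and a sensitivity/specificity range for binary ones. Use comparable ranges for M1 and M2, so that the analysis does not itself presume which is measured better.
3. Qualify any ranking of the mechanisms that does not hold across that range.

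The cost is a wording change and a modest extra analysis. Table 1 lists eight single-mediator and six two-mediator models, each for three outcomes, so restricting the work to the primary outcome and main models matters. The article describes no replicate or validation data, so the error ranges would have to be assumed and reported as such.

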## Conclusions

This study is designed to obtain and analyze additional data from the babies included in APTS to investigate the mechanism behind the reduced need for red cell transfusions. The analysis may also suggest other changes in clinical care that could reduce the need for transfusion. The outcomes of this study will directly address the research gap in relation to the role of routine use of deferred cord clamping for preterm newborn babies. As a result, the quality of guidance in relation to umbilical cord management and patient blood management in preterm babies is expected to improve.
